### Ethics

The study was approved by the regional ethics review board in Stockholm, Sweden (Dnr: 2017/124–31/2, 2018/2224–32) and The London Brent Research Ethics Committee (REC), UK (reference number: 18/LO/1190). The study is conducted in accordance with the Helsinki declaration and good clinical practice.

### Trial registration

The protocol is registered and published at ClinicalTrials.gov Identifier: NCT05628701.

### Study outline

#### Recruitment

After colectomy, patients will receive standardized written as well as oral information from a consultant regarding the collection of QoL measurements, functional scores and the different treatment modalities before being asked for consent to participate in the study. The patient will be prescribed topical 5-ASA according to local principles, usually 500–1000 mg twice daily. 3–6 months after the colectomy patients will be subjected to rectal endoscopic examination to assess rectal inflammation and compliance and sphincter function. Inflammation is assessed by Mayo score while the assessment of rectal compliance and sphincter function is based on patient history and the subjective evaluation by the responsible surgeon. Based on these factors it is determined if the patient is eligible for IRA as well as IPAA. Patients that are deemed eligible for both reconstructions, and otherwise fulfill inclusion criteria, will be analyzed in the study arms and will henceforth be referred to as the study arms in contrast to the controls (Fig. 2).

**Fig. 2 Fig2:**
[figure not shown]
Flow chart describing the selection of patients eligible for the study (green). The other patients (yellow) will be asked to participate as controls

#### IRA

The IRA can be performed both as an open or laparoscopic procedure, of which the latter is more common and preferred in modern practice. The ileostomy is closed, and the neoterminal ileum is in most cases anastomosed to the tip of the rectal remnant in the abdomen using a circular transanal stapling device or in some cases a handsewn anastomosis will be performed. The reconstruction is rarely protected by a temporary diverting loop ileostomy.

#### IPAA

The IPAA can be performed both as an open or, preferably as a laparoscopic or robotic procedure. A trans-anal minimal invasive method (TaTME) may be used to facilitate proctectomy [16]. A pouch is constructed with the last part of the distal ileum and then anastomosed to the anal canal, or to a small rectal remnant, usually 1–2 cm in length, often referred to as the rectal cuff. The anastomosis is often created with a transanal circular stapling device but can also be hand sutured if needed. In most, but not all cases, the reconstruction is protected by a temporary loop ileostomy. In those instances, the loop closure, when bowel continuity is restored, will be considered the index operation in the study. Technical aspects of the creation of the pouch was at the discretion of the individual surgeon, however recorded in the clinical report form.

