#### Time frame

Baseline data will be collected after colectomy for all patients. The reconstructed patients will then be followed at 2 months, 6 months, 1 year, 2 years and 5 years. Those patients that receive a loop ileostomy at reconstruction will also be followed 2 months after reconstruction before closure of the loop. For those patients the loop closure is considered the index operation. The patients that choose to (or are deemed to) keep their end ileostomies will be followed at 6 months, 1 year, 2 years and 5 years after colectomy (Fig. 3). The recruiting of patients started in March 2017.

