### Statistical analysis

Analysis will be conducted according to the intention-to-treat principal. The primary outcome satisfaction, a proportion, will be compared with chi-square test. For the primary outcome two-tailed tests will be applied since the null hypothesis is that there is no difference between the two reconstructive methods. Secondary outcomes assumed to be normally distributed will be compared between the two study arms using t-tests. Functional and QoL variables will be analyzed with mixed model ANOVA analysis. Time to failure will be analyzed with multivariate cox-regression analysis. Kaplan–Meier curves will be constructed and compared with log-rank tests. Repeating events, such as reoperations, will be analyzed with multivariate Poisson-regression.

There is no data and safety monitoring committee since all treatment is according to established practice. We do not plan to perform any interim analysis.

From a statistical point of view our choice of primary endpoint is not optimal because we have no reason to expect any difference between the two study arms. Still, to our opinion, this is the most important outcome measure.

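### Loop closure as the index operation gives the two arms different time origins in practice; if failure and reoperations run from it, IPAA is favoured and a never-closed pouch has no index date

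*Protocol article*

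**What the plan says.** The IPAA section of the protocol article says of diversion: "In most, but not all cases, the reconstruction is protected by a temporary loop ileostomy". For those patients, "the loop closure, when bowel continuity is restored, will be considered the index operation in the study". The Time frame section repeats the rule for any reconstructed patient given a loop: "For those patients the loop closure is considered the index operation". For IRA the article says: "The reconstruction is rarely protected by a temporary diverting loop ileostomy".

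The visit schedule is: "The reconstructed patients will then be followed at 2 months, 6 months, 1 year, 2 years and 5 years". Patients with a loop "will also be followed 2 months after reconstruction before closure of the loop".

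The Statistical analysis section states: "Time to failure will be analyzed with multivariate cox-regression analysis". It adds Kaplan–Meier curves with log-rank tests, and Poisson regression for repeated events such as reoperations. It names no time origin for any of these. It also states: "Analysis will be conducted according to the intention-to-treat principal". The Failure section applies the same principle to patients converted from either reconstruction to a permanent ileostomy.

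**The concern.** The rule follows the loop, not the arm, so the rare diverted IRA patient also starts at closure. Because diversion is usual for one operation and rare for the other, the rule still separates the arms. Nearly every IRA patient is at risk from the anastomosis onward. Most IPAA patients enter only after the pouch has been built, has healed and has been put into circuit.

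If time to failure and reoperations are counted from this index, the IPAA arm is conditioned on early success. Strictly, this is selection by reaching closure rather than classic immortal time, because the period before closure is left out and not credited to IPAA. The direction is clear: it lowers IPAA failure and reoperation rates relative to IRA.

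A pouch that is never closed has no index date at all. Its visits from 2 months to 5 years cannot be placed, and those visits also carry the satisfaction question, which is the primary endpoint. The patients affected would be those with the worst IPAA course, in a comparison meant to inform patients' choice.

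**Working it through.** **Reading the sections together**

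1. Index for diverted patients: loop closure, stated for the study as a whole and not limited to bowel function (IPAA; Time frame).
2. Who is diverted: most IPAA, few IRA (IPAA; IRA). No percentages are given.
3. Failure: the Discussion describes it as excision or permanent diversion. A pouch never put into circuit fits that description once diversion is permanent, and the Failure section keeps such a patient in the assigned arm.
4. From 1 and 3, the same patient is an intention-to-treat failure but has no index date. The schedule for patients who keep an end ileostomy, counted from colectomy, does not clearly apply either, because this patient has been reconstructed and has a loop.
5. Before closure there is one visit, 2 months after reconstruction, and perioperative complications are recorded for each operation (Data collection). Events before closure are therefore at least partly collected. The problem is where they lie relative to time zero.

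**Scale from the article's own figures**

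The article gives no figure for failure before closure. Its sample size calculation does not bear on this point. The usable inputs are the target of 50 per group (Sample size) and the cited 5-year failure of 4–9% for IPAA and 10–16% for IRA (Discussion).

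- Expected IPAA failures at 5 years: 50 × 0.04 = 2 to 50 × 0.09 = 4.5.
- One never-closed pouch left out: 1/4.5 = 22% to 1/2 = 50% of those failures.

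**Illustration under assumptions that the article does not give**

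Assume a diverted share q of 60–90%, and a proportion f of 1–4% of diverted pouches failing before closure or never closed. Let F be 5-year IPAA failure counted from pouch construction, and ignore the small shift of the 5-year horizon.

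- Failures before time zero in 50 patients = 50·q·f: from 50 × 0.6 × 0.01 = 0.3 to 50 × 0.9 × 0.04 = 1.8.
- Apparent failure from closure = (F − qf)/(1 − qf).
  - F = 9%: (0.09 − 0.006)/0.994 = 8.5% down to (0.09 − 0.036)/0.964 = 5.6%.
  - F = 4%: (0.04 − 0.006)/0.994 = 3.4% down to (0.04 − 0.036)/0.964 = 0.4%.
- IRA:IPAA hazard ratio with constant hazards = ln(1 − IRA failure)/ln(1 − IPAA failure).
  - 10% against 9%: ln 0.90/ln 0.91 = 1.12 from reconstruction; 1.19 to 1.83 with the apparent IPAA figures.
  - 16% against 9%: 1.85 from reconstruction; 1.97 to 3.02 with the apparent figures.
  - With F = 4% the ratio becomes unstable at the upper end, because nearly all IPAA failures would then precede closure.

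**The case against.** The strongest reply is that the clock for failure is inferred. The Statistical analysis section names no origin, and the index rule stands in the surgical description and beside the visit schedule, where it may serve only to place questionnaires. An analysis plan that is not shown could set another origin. This stands as a limit: a reader might infer that the protocol fixes the survival clock at loop closure, and it does not say so outright. But it calls loop closure the study's index operation without restriction and offers no alternative, so an analyst who follows the text would use it.

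A reader might also infer that major complications of pouch construction are lost: at the cited 10–18% after IPAA, 50 × 0.10 = 5 to 50 × 0.18 = 9 patients. The article does not support this. Perioperative complications are recorded for each operation, and the Discussion describes early complications as those within 30 days of surgery, not of the index. The problem arises only if they are counted from the index operation alone.

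Nor does the article say that never-closed pouches are dropped. The intention-to-treat wording keeps them. What is missing is an index date and a visit schedule that would let that wording be carried out.

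Finally, time to failure is not among the endpoints listed in the Endpoints section, and restored continuity is a sensible anchor for function. Both points are correct and limit the weight of the concern. They do not remove it, because failure is given a planned between-arm analysis and the missing visits reach the primary endpoint.

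**Conclusion.** The concern holds in a conditional form. The index rule gives the arms different origins in practice. If failure and reoperations run from the only origin that the article names, the comparison favours IPAA, and a never-closed pouch cannot be analysed as the intention-to-treat rule requires.

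The size cannot be derived from the document. The 22–50% is the effect of one hypothetical patient and not a forecast. The range of 0.3 to 1.8 early failures in 50, and the hazard ratios built on it, rest on assumed diversion and non-closure rates, and the lower end is less than one patient. Against only 2 to 4.5 expected failures, however, a single patient matters. The Trial status section reports 11 IPAA patients in the study arms by September 2022, so each one currently weighs more still. The origin should be settled before analysis.

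**What to change.** - **Time to failure and reoperations:** start both arms at the first reconstructive operation (pouch construction or IRA). Keep never-closed pouches in the IPAA arm and count them as failures once diversion is permanent. Do not count planned loop closure as a reoperation.
- **Early complications:** report them over all stages of the reconstruction (pouch construction plus loop closure) against IRA.
- **Bowel function, quality of life, sexual function and satisfaction:** keep restored continuity as the anchor for these assessments. For patients never closed, date the satisfaction and quality-of-life assessments from the reconstruction, so that they stay in the intention-to-treat comparison.
- **Sensitivity analysis:** show failure from restored continuity. Time from pouch construction includes a diverted period in which failure from poor function cannot yet occur, which can itself flatter IPAA slightly; this analysis addresses it.

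The cost is mainly wording. Complications are already recorded per operation and a pre-closure visit exists. The article's list of variables does not name operation dates, so it should be confirmed that they are held for every stage. The questionnaires for never-closed patients are a small addition to data collection.

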#### Controls

In order to obtain a comprehensive overview of all UC patients that undergo colectomy, patients that decline reconstruction or those eligible only for one method of reconstruction (e.g. only IPAA due to refractory proctitis) will be asked to participate as controls.

#### Failure

Patients converted from IRA to IPAA or from either reconstruction to a permanent ileostomy will be analyzed in an “intention-to-treat” manner.

### Data collection

#### Instruments

General QoL will be assessed with the SF-36 form [17], IBD specific QoL with the SHS [18], bowel function with the Öresland score [19], female sexual function with the FSFI-6 [20], male sexual function with IIEF-5 [21]. In addition to these validated forms questions on whether or not the patients are satisfied with their choice of operation, would choose it again and recommend it to others and questions on fertility and reproduction will be asked. Early complications will be measured according to the Clavien-Dindo scale [22].

Data will also be obtained on smoking status, UC medication, age, indication for colectomy (chronic active disease/acute flare/dysplasia), BMI, endoscopic status in pouch/rectum, reoperations and for each operation: operation technique, operative time, bleeding, perioperative complications and hospital stay.

The data is collected and managed using REDCap (Research Electronic Data Capture) [23, 24] hosted at the Karolinska Institute, Stockholm, Sweden.

#### Time frame

Baseline data will be collected after colectomy for all patients. The reconstructed patients will then be followed at 2 months, 6 months, 1 year, 2 years and 5 years. Those patients that receive a loop ileostomy at reconstruction will also be followed 2 months after reconstruction before closure of the loop. For those patients the loop closure is considered the index operation. The patients that choose to (or are deemed to) keep their end ileostomies will be followed at 6 months, 1 year, 2 years and 5 years after colectomy (Fig. 3). The recruiting of patients started in March 2017.

**Fig. 3 Fig3:**
[figure not shown]
Timeline describing the collection of QoL and functional score questionnaires in the study population

### Statistical analysis

Analysis will be conducted according to the intention-to-treat principal. The primary outcome satisfaction, a proportion, will be compared with chi-square test. For the primary outcome two-tailed tests will be applied since the null hypothesis is that there is no difference between the two reconstructive methods. Secondary outcomes assumed to be normally distributed will be compared between the two study arms using t-tests. Functional and QoL variables will be analyzed with mixed model ANOVA analysis. Time to failure will be analyzed with multivariate cox-regression analysis. Kaplan–Meier curves will be constructed and compared with log-rank tests. Repeating events, such as reoperations, will be analyzed with multivariate Poisson-regression.

There is no data and safety monitoring committee since all treatment is according to established practice. We do not plan to perform any interim analysis.

From a statistical point of view our choice of primary endpoint is not optimal because we have no reason to expect any difference between the two study arms. Still, to our opinion, this is the most important outcome measure.

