### Study design

The CRUISE study is a prospective, non-randomized, non-blinded, multi-center, controlled trial on satisfaction, QoL, function, and complications between IRA and IPAA and permanent stoma among adult UC patients subjected to subtotal colectomy. All adult UC patients scheduled for a subtotal colectomy will be asked for informed consent. The patients will then be presented standardized written and video recorded information on the available reconstructive options. If the patient meets the inclusion criteria, their preferred choice of IRA or IPAA will assign them to one of the study arms. Patients that do not meet the inclusion criteria or fulfill any of the exclusion criteria (e.g. not suitable for an IRA) or refrain reconstruction will be asked to participate as controls.

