### Sample size

The only available study on patient satisfaction, our primary outcome, between IRA and IPAA reports 98% and 88% satisfaction for the methods respectively [15]. However, they only asked the IRA patients that still had their IRA in place after a mean of 11 years making it a little difficult to interpret. Another study compared QALYs between IRA and IPAA and reports a mean of 33.42 for IRA and a mean of 31.57 for IPAA [13]. With an estimated 3 SD (it was 2.8 for IRA and 4.5 for IPAA) and the significance level 0.05 and 80% power that difference would require 43 patients in each group to demonstrate a difference. Due to the mentioned shortcomings of the study comparing satisfaction we regard the latter study more relevant and decided to aim at a minimum of 50 patients in each group. Deliberately a little over the power estimation to avoid any effect of possible loss to follow-up.

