In reconstructive surgery, the goal is to improve quality of life (QoL). Still, it is not obvious how to assess and compare QoL in surgery for UC [63]. In studies comparing IPAA to end ileostomy, an improved body image was reported among the IPAA patients but otherwise similar satisfaction and QoL [64-67]. There are several studies investigating how QoL develops over time in IPAA patients. It appears that the QoL of the IPAA patients is somewhat impaired in the first months after surgery but then improves [68, 69] and the QoL of the IPAA patients appears to be good in the long-term [42, 70]. Available studies comparing QoL in IRA to IPAA reports similar [15, 71] QoL between the two procedures but one study reported more urgency affecting work and dietary restrictions among the IRA patients [72].

Failure, defined as excisions or permanent deviation, is reported in between 4–9% of IPAA cases at 5 years and 7–19% at 10 years [30, 73-78] and reports with longer follow up indicates a continuing annual failure rate of around 2% even after 15 years [79]. The reported failure rates for IRA are 10–16% at 5 years and 24–31% at 10 years [30, 34, 39, 80, 81]. One should remember that after excising a poorly functioning IRA it is possible to construct an IPAA. However, the options after excising an IPAA are either a redo IPAA or an end ileostomy [82].

The obvious limitation with our study design is the lack of randomization. As mentioned in the introduction we have made an attempt to randomize between IRA and IPAA but after receiving detailed information, patients decline randomization and insist on choosing a reconstructive method themselves, with similar numbers opting for IRA and IPAA. We do not consider it a risk, but a fact, that some degree of selection bias will occur as some patients are more concerned regarding pelvic surgery, and its possible consequences, while others are more concerned by the need of anti-inflammatory medication, endoscopic surveillance and the risk of rectal cancer. We aim to minimize such effects with the provision of standardized information whenever possible. Because this is a multicenter study the same consultant cannot present the oral information to every patient. Instead, all patients will be shown the same information video by the consultant IBD Surgeon.

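### Satisfaction is compared by an unadjusted chi-square between arms that patients chose themselves; a small pre-specified adjusted estimate should lead instead

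*Protocol article*

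**What the plan says.** **Allocation.** Under Study design, patient preference forms the arms: "their preferred choice of IRA or IPAA will assign them to one of the study arms".

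**Primary analysis.** Under Statistical analysis: "The primary outcome satisfaction, a proportion, will be compared with chi-square test". The test is two-sided: "For the primary outcome two-tailed tests will be applied since the null hypothesis is that there is no difference". No covariate, stratum or weight is named for it. The same paragraph plans multivariate Cox regression for time to failure, multivariate Poisson regression for repeated events such as reoperations, and a mixed-model ANOVA for functional and QoL variables.

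**Selection.** The Discussion is candid: "We do not consider it a risk, but a fact, that some degree of selection bias will occur". The remedy named there is the standardised information, including a common video. The Study population and Recruitment sections add a second control, because the study arms hold only patients judged suitable for both operations.

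**Data available for adjustment.** Under Instruments: "Data will also be obtained on smoking status, UC medication, age, indication for colectomy", followed by BMI and endoscopic status among others. The Time frame section plans baseline data after colectomy for every patient.

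**The concern.** A two-group chi-square p-value is calibrated for arms that differ only by chance. Here they differ by choice, and the protocol itself hopes to find demographic patterns in that choice. If a characteristic that affects satisfaction also affects which operation is chosen, the crude difference combines the effect of the operation with the make-up of the arms. It can create a difference or hide one. The second risk matters because the authors expect the two methods to be equally good in this population, so a crude null result could be read as confirming that.

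The stated objective is comparative and the authors hope to influence treatment recommendations. Multivariate modelling is already planned for failure and reoperations, so the primary outcome gets less protection against confounding than those secondary ones.

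**Working it through.** **1. The protocol's own figure.** The Sample size section states: "the significance level 0.05 and 80% power that difference would require 43 patients in each group to demonstrate a difference". Inputs: QALY means 33.42 and 31.57, difference 1.85, SD 3, two-sided alpha 0.05, power 80%.
- Normal approximation: n = 2 × [3 × (1.960 + 0.842) / 1.85]² = 41.3, so 42 per group.
- Two-sample t-test: 42.26, so 43 per group, as stated.

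The arithmetic is sound. The point concerns the analysis method. The planned minimum is 50 per group.

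**2. Bias from one unbalanced factor (assumed values).** The documents give neither an imbalance nor a link between a covariate and satisfaction, so both are assumptions. Let the factor be present in 60% of one arm and 30% of the other, with no effect of the operation.

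Arm rate = prevalence × rate with factor + (1 − prevalence) × rate without. Gap = (0.60 − 0.30) × (difference in satisfaction by factor).

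| Satisfaction with / without factor | Arm rates | Gap |
|---|---|---|
| 95% / 85% | 0.60×95 + 0.40×85 = 91.0%; 0.30×95 + 0.70×85 = 88.0% | 3.0 points |
| 95% / 80% | 0.60×95 + 0.40×80 = 89.0%; 0.30×95 + 0.70×80 = 84.5% | 4.5 points |

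**3. Effect on the planned test.** For x and y satisfied out of 50 and 50, X² = (x/50 − y/50)² / [p̄(1 − p̄)(1/50 + 1/50)], with p̄ = (x + y)/100. The exact rejection probability sums Bin(x; 50, p₁) × Bin(y; 50, p₂) over all pairs with X² > 3.84.

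| Arm rates | Rejection with bias | Rejection if both arms are at the mean rate |
|---|---|---|
| 91.0% v 88.0% | 7.9% | 5.1% (at 89.5%) |
| 89.0% v 84.5% | 10.8% | 5.5% (at 86.75%) |

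**4. Sensitivity to the assumption (normal approximation, 50 per arm).**

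| Factor prevalence by arm | Satisfaction with / without | Gap | Rejection |
|---|---|---|---|
| 60% / 40% | 98% / 88% | 2 points | 6.8% |
| 70% / 30% | 98% / 88% | 4 points | 12.2% |
| 80% / 20% | 95% / 70% | 15 points | 50.6% |

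The last row is an extreme case. More patients do not help: in the first row, rejection rises from 6.8% to 12.3% at 200 per arm, because the bias stays while the standard error shrinks.

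**5. How much adjustment the data can carry.** At the cited satisfaction rates of 98% and 88%, the expected number dissatisfied is 50 × 0.02 + 50 × 0.12 = 1 + 6 = 7. Trial status reports 37 IRA and 11 IPAA patients in the study arms, 48 in all, so 37/48 = 77% chose IRA. Neither figure supports an outcome regression or a propensity model with many covariates.

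**The case against.** The best defence is the design. Study-arm patients are aged 18 to 60 and suitable for both operations. Mayo score above 1, poor sphincter function, perianal disease, uncertain diagnosis, previous cancer or severe dysplasia, PSC and more than two years since colectomy are all excluded. Patients suitable for only one method become controls. This removes much confounding by indication, so it would be wrong to infer that standardised information is the only safeguard. Restriction does not, however, equalise sex, country, indication or baseline QoL between those who choose each operation.

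The limitation is openly disclosed, and supporting adjusted analyses may sit in a plan not shown here. Both are fair points and they lower the severity. Disclosure does not change the estimate, though, and the article does name the test for the primary outcome.

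Three stronger readings are tempting but unsupported:
- **That QoL and function get bare t-tests.** The sentence "Secondary outcomes assumed to be normally distributed will be compared between the two study arms using t-tests" invites this, but the next one assigns functional and QoL variables to the mixed-model ANOVA.
- **That the covariates collected would remove the bias.** The Discussion names what drives choice: worry about pelvic surgery on one side, and about medication, surveillance and rectal cancer on the other. Instruments lists no measure of these attitudes, which could plausibly bear on satisfaction with one's choice.
- **That the assumed factor pushes false rejection to about 13%.** Gaps of 3.0 and 4.5 points centred on 93% satisfaction do give 8.1% and 12.9%, but the assumed factor implies means of 89.5% and 86.75%, where the figures are 7.9% and 10.8%.

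**Conclusion.** The point holds in a limited form. The protocol specifies an unadjusted test as its primary comparison of self-selected arms, while accepting that selection bias will occur and planning multivariate models for failure and reoperations. Followed as written, the primary result is not an estimate for comparable patients.

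The size is illustrative only. Under a moderate assumed imbalance the gap is 3.0 or 4.5 points, with false rejection near 8% or 11% instead of about 5%. Weaker or stronger assumptions move this widely, and the documents cannot say which applies or in which direction. They do not show that the trial will reach a wrong answer, nor that adjustment would make the arms fully comparable. This should be fixed, as a cheap improvement rather than a defect that invalidates the study.

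**What to change.** Pre-specify as the primary estimate a confounder-adjusted risk difference in satisfaction (IRA v IPAA) with a 95% confidence interval:
- Use a short list of baseline covariates, for example age, sex, indication for colectomy, country and baseline QoL. Age and indication are listed as collected. Sex and country should be known from the sex-specific questionnaires and the two-country setting, and baseline QoL falls under the planned baseline assessment. Endoscopic status may enter only as the value before reconstruction.
- Apply these through a parsimonious or penalised propensity-score weighting model with robust standard errors. Weighting is preferable to outcome regression because so few dissatisfied patients are expected.
- Keep the chi-square as the unadjusted supporting result.
- State that the attitudes named as driving choice are not listed as measured, that residual confounding therefore remains, and limit causal wording accordingly.

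**Cost.** Analysis wording and modest extra work, with no new data. The interval will be wider, more so if the IPAA arm stays small (37 v 11 so far), and the covariate list must then be kept very short. If overlap weights are used, the target population changes to patients with a realistic chance of choosing either operation, and the report should say so.

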### Endpoints

The primary endpoint is satisfaction with the choice of reconstructive method or permanent stoma. Secondary endpoints are QoL, sexual function, bowel function and complications.

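### QoL and sexual-function scores fall under both unadjusted t-tests and a mixed model, and the pre-reconstruction score has a stated role in neither

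*Protocol article*

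**What the plan says.** The Endpoints section of the protocol article states: "Secondary endpoints are QoL, sexual function, bowel function and complications". Under Instruments, "General QoL will be assessed with the SF-36 form"; the other scores are SHS (IBD-specific QoL), Öresland (bowel function), FSFI-6 and IIEF-5 (sexual function).

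Two consecutive sentences of the Statistical analysis section apply to these scores. The first is "Secondary outcomes assumed to be normally distributed will be compared between the two study arms using t-tests". The second is "Functional and QoL variables will be analyzed with mixed model ANOVA analysis". Multivariable models are named only for time to failure (Cox) and for recurrent events such as reoperations (Poisson).

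The Time frame section states "Baseline data will be collected after colectomy for all patients" and continues "The reconstructed patients will then be followed at 2 months, 6 months, 1 year, 2 years and 5 years". The QoL and sexual-function scores therefore have one measurement before reconstruction and five after it.

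Allocation is by patient choice. The Study design section says that "their preferred choice of IRA or IPAA will assign them to one of the study arms". The Discussion accepts that some selection bias is certain and gives as one reason that "some patients are more concerned regarding pelvic surgery, and its possible consequences".

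**The concern.** A two-sample t-test on a follow-up score asks whether two self-chosen groups have the same mean level. If they already differed before reconstruction, they can differ afterwards even when the operations have identical effects. Choice is said to depend partly on concern about pelvic surgery, and the Discussion names impaired sexual function as a risk of pelvic dissection. A prior difference in sexual-function scores is therefore plausible, although the article does not report one.

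The mixed model may or may not deal with this, because the section does not say whether baseline is a covariate, a visit or left out. If it is a visit and the group main effect is reported, a visit made before treatment is averaged into the contrast.

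Two things are at stake. A pre-existing difference could be reported as an effect of the operation, or could hide one. Power is also lost even if the arms happen to be balanced, although the score that would recover it is already being collected.

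**Working it through.** **The plan's own figure.** The only sample-size calculation concerns QALYs: 33.42 − 31.57 = 1.85, SD 3, standardized difference 1.85/3 = 0.617, two-sided 5%, 80% power. The t-based calculation gives 42.26, rounded up to 43 per group, which reproduces the stated 43. It is not about these questionnaire scores, so the effect sizes below are assumptions.

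**Inputs from the article.** Target of at least 50 per arm (Sample size); one baseline and five follow-up visits (Time frame); 37 IRA and 11 IPAA patients in the study arms in September 2022 (Trial status).

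**Assumptions not in the article.** Normal scores with SD 1; the same correlation r between any two visits, r = 0.4 to 0.7; complete data; two-sided 5%. Power is for a true effect of 0.5 SD with balanced arms. False rejection is for no operation effect and a prior gap of 0.3 SD that persists at every visit.

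**Formulas.** SE = √[V(1/n₁ + 1/n₂)], referred to the non-central t distribution. The small increase in the adjusted SE caused by the baseline gap itself is ignored.
- One visit, unadjusted: V = 1
- One visit, baseline-adjusted: V = 1 − r²
- Mean of five visits, unadjusted: V = r + (1 − r)/5
- Mean of five visits, baseline-adjusted: V = r + (1 − r)/5 − r²
- Bias from the gap: 0.3 unadjusted; 0.3(1 − r) adjusted

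**Worked case**, r = 0.6, 50 per arm (1/50 + 1/50 = 0.04). Unadjusted at one visit: SE = √0.04 = 0.200; 0.5/0.200 = 2.50, power 70%; 0.3/0.200 = 1.50, false rejection 32%. Adjusted at one visit: SE = √(0.64 × 0.04) = 0.160; 0.5/0.160 = 3.13, power 87%; 0.12/0.160 = 0.75, false rejection 11.5%.

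Power (%), balanced arms, 0.5 SD effect:

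| r | One visit, unadjusted | One visit, adjusted | Five-visit mean, unadjusted | Five-visit mean, adjusted |
|---|---|---|---|---|
| 0.4 | 69.7 | 77.1 | 93.0 | 98.5 |
| 0.5 | 69.7 | 81.5 | 89.2 | 98.7 |
| 0.6 | 69.7 | 87.2 | 85.1 | 99.2 |
| 0.7 | 69.7 | 93.4 | 81.0 | 99.7 |

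False rejection (%), no operation effect, persistent 0.3 SD prior gap:

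| r | One visit, unadjusted | One visit, adjusted | Five-visit mean, unadjusted | Five-visit mean, adjusted |
|---|---|---|---|---|
| 0.4 | 31.8 | 16.3 | 54.0 | 31.8 |
| 0.5 | 31.8 | 13.8 | 48.3 | 24.1 |
| 0.6 | 31.8 | 11.5 | 43.7 | 18.3 |
| 0.7 | 31.8 | 9.6 | 39.9 | 13.8 |

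**Group main effect with baseline as a sixth visit.** V = r + (1 − r)/6, and the effect shrinks to 5/6 × 0.5 = 0.417. Power is 66–83% and false rejection 40–56%. This applies only if that contrast is the one reported.

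**Milder scenario.** If only the part of the gap correlated with baseline carries over, the t-test's bias is 0.3r = 0.12 to 0.21 SD and it rejects 9–18% of the time. The baseline-adjusted comparison is then unbiased.

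**Enrolment so far**, r = 0.6, 1/37 + 1/11 = 0.1179, 0.5 SD effect. One visit: power 30% unadjusted, 43% adjusted. Five-visit mean: SE = √(0.68 × 0.1179) = 0.283, power 41% unadjusted; SE = √(0.32 × 0.1179) = 0.194, power 71% adjusted.

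**The case against.** The strongest objection is that the mixed-model sentence is the more specific one and naturally governs these scores, with t-tests left for operative time, bleeding and hospital stay. If baseline is a visit in that model, the arm-by-time contrast does use each patient's own baseline. This stands as far as it goes. A reader might infer from the t-test sentence that QoL and sexual function will be compared by t-test alone and that baseline is ignored; the article does not support that. Nor does it say that the group main effect will be reported. What remains is that the t-test sentence, read with the Endpoints list, also covers these scores, and the article does not say which sentence governs.

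A second stronger reading is that adjusting for baseline would isolate the effect of the operation. It would not. At r = 0.4 the adjusted five-visit mean still rejects falsely 32% of the time in the persistent-gap scenario, as often as the single-visit t-test. Its fair comparator is the unadjusted five-visit mean, at 54%. Likewise, setting the 66–83% power of the main effect against 98.5–99.7% would overstate the gain. Like for like, it is about 6–19 points over five visits.

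Third, the gap and r are assumed. The Discussion says that patients differ in their concerns, not that their baseline scores differ. It also reports similar QoL in existing comparisons, so the article gives no ground for expecting a QoL difference; only sexual function has some support there.

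Finally, model detail is commonly left to a SAP or full protocol, and neither is shown. This limits the weight of the point. It does not dispose of it, because an unadjusted t-test is a method that the article names, not one that it leaves open.

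**Conclusion.** The point holds in a limited form. The Statistical analysis section names two methods for overlapping endpoints, one of them unadjusted, and gives the collected baseline score no stated role, in a comparison where patients choose their arm and selection bias is accepted as certain.

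Under the stated assumptions at 50 per arm, adjustment adds about 7–24 points of power at one visit (70% to 77–93%). With a persistent 0.3 SD prior gap, it cuts false rejection to between one third and three fifths of the unadjusted rate. It reduces the bias without removing it. The sizes depend on r and on a gap that the article does not give. The point concerns secondary endpoints only, and an unseen analysis plan may already settle the model. It is a worthwhile, nearly free correction and does not threaten the primary comparison.

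**What to change.** In the Statistical analysis section, name one analysis for SF-36, SHS, FSFI-6 and IIEF-5: a mixed model with the follow-up visits as outcomes, the patient's own post-colectomy score as covariate, and arm, visit and arm-by-visit terms, reporting the baseline-adjusted arm difference. Add change from baseline as a sensitivity analysis. In the persistent-gap scenario it has no bias and rejects about 5% of the time.

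Restrict t-tests to outcomes that have no baseline, such as operative time and hospital stay. Leave the Öresland score out of the baseline adjustment, since patients have an ileostomy when baseline is taken. State that confounding by choice remains after adjustment.

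The cost is a few sentences and no new data. Missing baseline questionnaires will need a stated method of handling, and the adjusted and change analyses may disagree somewhat.
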